#### Brief Symptom Inventory-18

The Brief Symptom Inventory-18 (BSI-18) [62] is an 18-item measure that assesses the level of distress a person has experienced in the past day due to various psychological (eg, feelings of worthlessness) and physical (eg, pains in the heart or chest) symptoms. Questions are responded to on a 5-point scale from 0 (not at all) to 4 (extremely) and can be summed to produce 3 subscale scores (depression, anxiety, and somatization) as well as a global severity index that measures overall psychological distress. The BSI-18 has been validated and normed with community samples and is acceptable to use repeatedly as a measure of symptom change [63]. The BSI-18 is administered nightly during the 7-day intensive data collection phase of this study.

#### Daily Positive and Negative Mood Questionnaire

Aspects of participants’ daily mood are assessed using a version of the Positive and Negative Affect Schedule [64] described by Smyth et al [65]. Participants rate their current level of 4 positive and 5 negative mood adjectives on a 7-point scale anchored by 0 (not at all) and 6 (extremely). Items are summed to produce positive and negative mood subscales that demonstrated acceptable psychometric properties in a previous sample of community participants [65]. This measure is administered nightly during the 7-day intensive data collection phase of this study.

#### Daily Events Questionnaire

The Daily Events Questionnaire asks individuals to select from a list of common daily stressors (eg, a lot of work at school or work or a financial problem) and people (eg, a friend or spouse) to assess if any troublesome events happened to them since they woke up that morning, as well as if they experienced any tension or arguments with anyone. Individuals can select as many options as apply and have the option to describe any “other” event or relationship not listed. For each selected event, individuals are then asked to indicate approximately when this event occurred and how distressed they felt during the event, from 1 (not at all) to 10 (very much). Similarly, for each person that a participant indicates they had an argument with, they are asked to provide approximately when the argument began and ended, as well as how distressed they felt and how satisfied they felt with the outcome of the event (using the same 10-point response scale). This measure has been used previously to successfully identify the approximate timing of various distressing events throughout the day [66]. In this study, it is administered nightly during the 7-day intensive data collection phase of this study.

#### Daily Call With Study Staff

Study staff calls participants each evening near the end of the day (ie, between 6 PM and 8 PM) to inquire about compliance with study procedures, problems with study equipment, and the nature and timing of participants’ most positive and negative events of the day. A transcript of the semistructured interview questions used during these phone calls is available on our Open Science Foundation site [53].

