### Procedures

Participants are recruited using web-based advertising through the University of Utah websites, social media websites, and listserves, as well as paper fliers posted throughout the Salt Lake City area. Interested participants complete a web-based screening survey to determine eligibility. Eligible participants are then forwarded to an electronic consent form, and consenting participants complete another web-based battery of questionnaires to assess current and lifetime psychiatric and medical diagnosis and treatment, current psychological symptoms and social functioning, and demographic variables. Participants who complete this baseline battery are compensated US $25 and are scheduled for a videoconference call during which study staff instructs them on how to use the study equipment (ie, audio recorder) that is mailed to them.

Following this call, participants begin a continuous 7-day period of intensive data collection that includes wearing the audio recorder during waking hours, providing raw sensor data collected through a smartphone app (Beiwe [50]), completing a brief survey to assess mood and important events at the end of each day, and responding to a brief phone call from study staff every evening. During this phone call, study staff assess compliance with study procedures, ask participants to describe the most positive and negative events from that day, and inquire whether there is any period of the recording from that day that they wish to delete. Providing participants the opportunity to review the contents of their recordings is necessary to meet ethical standards for long-term, ambulatory data collection [51]. After returning the audio recorder, participants are compensated US $10 and US $4.28 for every day that they provided raw sensor (PDD) data and audio recording, respectively.

Participants also complete web-based questionnaires 6 and 12 months after the 7-day intensive data collection phase to reassess current psychological symptoms and social functioning, as well as psychiatric and medical diagnosis and treatment during the intervening time; they are compensated US $20 for the completion of each of these questionnaires. See Figure 1 for the complete procedure flow diagram. All of these procedures are described in more depth below.

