#### Audio Data

In situ audio is continuously recorded while participants are awake at 24-bit/48 kHz using omnidirectional Lavalier microphones connected to miniature field recorders. Recordings are segmented into smaller, 15-minute-long files to optimize data transfer and increase data processing efficiency.

We have carefully considered legal and ethical issues in proposing these in situ recordings. Audio recordings are governed by wiretapping laws, which vary from state to state. Utah is a single-party consent state, meaning that as long as a study participant consents to be recorded, other individuals captured on those recordings do not need to additionally consent. However, the ethical principles of beneficence, nonmaleficence, autonomy, and justice require that other individuals who may be recorded need to be aware of that possibility and given the opportunity to not be recorded. For these reasons, participants are instructed to wear a badge that states that they are participating in a study that records audio during daily life and will be allowed to pause the recording whenever an individual they come into contact with requests that they do so, or the participant wishes or is required to do so by policy or law [51]. We have used these methods in previous work, and they typically generate 10 to 14 hours of audio per day.

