### Planned Data Processing

Raw item responses as well as relevant total and subscale scores from the self-report questionnaires will be created using standard scoring protocols and included for all self-report measures in the final data set. In addition to raw DERS scores, age- and gender-adjusted *t*-scores computed using the methods in [55] will be included in the final data set. Annotations of participants’ most positive and negative daily events will also be available in the data set. To create these, study staff will use the information provided by participants during the daily phone calls to annotate details about their most positive and negative event for each day, including the beginning and end time of the event, and the type (eg, interaction with another person or financial problem) and nature of the event (eg, positive vs negative). Study staff will additionally annotate speaker IDs (eg, participant and female 1), emotional expressions, and communication behaviors (eg, arguing or cooperating) using information from the corresponding recorded audio.

Audio recordings will be processed to generate gold-standard acoustic feature sets used in behavioral signal processing [68] and affective computing [69] research using the openSMILE toolkit [70]. These methods produce 88 acoustic variables that represent frequency-, energy-, and spectral-related aspects of speech and ambient noise. Acoustic variables will be generated over the smallest window of time possible for each variable and downsampled to produce a summary score for each acoustic variable for each 1 second of the recording.

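### As described, the 6 to 8 PM call asks only about the same day, so events and audio between the call and the end of recording fall outside both the event annotation and the deletion offer

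*Protocol article*

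**What the plan says.** The section Daily Call With Study Staff fixes the time of contact: "Study staff calls participants each evening near the end of the day (ie, between 6 PM and 8 PM"). Procedures says that in this call staff "ask participants to describe the most positive and negative events from that day" and also "inquire whether there is any period of the recording from that day that they wish to delete". The same section gives the reason for the second question: "Providing participants the opportunity to review the contents of their recordings is necessary to meet ethical standards for long-term, ambulatory data collection".

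Audio Data sets the recording period: "In situ audio is continuously recorded while participants are awake". Of the same methods in previous work it reports that "they typically generate 10 to 14 hours of audio per day".

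Planned Data Processing makes the calls the source of the event annotations. Staff will use them to "annotate details about their most positive and negative event for each day", including start and end times, and will then label speakers, emotional expression and communication behavior from the matching audio.

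**The concern.** The call looks back over a day that is not finished, while the recorder keeps running. Two products of the study depend on the call.

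- **Event annotation.** If a stronger positive or negative event happens after the call, the annotated event is not the most extreme one of that day, although it is labelled as such. The omission depends on clock time, so it is systematic: late-day events cannot be chosen. The daily sensor summaries carry no such cut-off, so a user who pairs the two by day compares a part-day label with a whole-day summary.
- **Deletion offer.** Audio recorded after the call goes into processing without the retrospective offer. Acoustic summary features are to be publicly downloadable under a brief data use agreement, and raw audio is to be available to approved users under stricter conditions.

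**Working it through.** **Step 1: set the stated periods side by side.**

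| Element | Period covered | Section |
|---|---|---|
| Audio recording | All waking hours | Procedures; Audio Data |
| Event question in the call | That day, asked at 6 to 8 PM | Procedures; Daily Call With Study Staff |
| Deletion question in the call | That day's recording, asked at 6 to 8 PM | Procedures |
| Staff annotation | Labelled as each day, built from the calls | Planned Data Processing |
| Daily Events Questionnaire | From waking to completion; troublesome events and arguments only | Daily Events Questionnaire |

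Time after the call on day *d* has not yet happened when the day-*d* question is asked, and it does not belong to day *d*+1 when the next question is asked. After the last call the article describes the return of the recorder, but no further question about events or deletion.

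**Step 2: size from the article's audio yield.** The article gives no start time, so starts of 6 to 9 AM without pauses are assumed. Audio after the call = max(0, start + hours of audio − call time).

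| Start | Audio (h) | End | After 6 PM call | After 8 PM call |
|---|---|---|---|---|
| 6 AM | 10 | 4 PM | 0 h | 0 h |
| 6 AM | 14 | 8 PM | 2 h | 0 h |
| 7 AM | 10 | 5 PM | 0 h | 0 h |
| 7 AM | 14 | 9 PM | 3 h | 1 h |
| 8 AM | 10 | 6 PM | 0 h | 0 h |
| 8 AM | 14 | 10 PM | 4 h | 2 h |
| 9 AM | 10 | 7 PM | 1 h | 0 h |
| 9 AM | 14 | 11 PM | 5 h | 3 h |

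The range is 0 to 5 hours per day, at most 5/14 = 36% of that day's audio. It is zero for a 10-hour recording that starts at 8 AM or earlier. A pause before the call moves the end of recording later for the same yield: with a 7 AM start and 12 hours of audio, a 2-hour pause before 6 PM moves the end from 7 PM to 9 PM, and audio after a 6 PM call rises from 1 to 3 hours.

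**Step 3: size if recording lasts until bedtime.** Assume a bedtime of 10 PM to midnight and 16 waking hours. Hours after the call = bedtime − call time.

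- Smallest: 22 − 20 = 2 h (2/16 = 12.5%).
- Largest: 24 − 18 = 6 h (6/16 = 37.5%).
- Over 7 days: 7 × 2 = 14 h to 7 × 6 = 42 h per participant.

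**The case against.** The strongest reply is that the article only summarizes the call. The semistructured interview questions are posted elsewhere and are not shown here. They may ask about the time since the previous call, and nothing in the article forbids a participant from naming a stretch of the previous evening. This stands to the extent that one cannot say post-call time is *never* covered. It does not remove the point: the article gives the reference period as the same day for both questions, and a next-day look-back would still leave the last evening without a question.

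Other safeguards exist, and each is partial.

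- The Daily Events Questionnaire belongs to the end-of-day survey and records approximate times of troublesome events and arguments. If completed after the call, it can capture later conflicts. It does not ask about positive events, makes no deletion offer, and is not the named source of the annotations.
- Participants may pause the recorder when they wish, but a pause must be chosen beforehand. The deletion offer serves second thoughts.
- Raw audio is under restricted access. That limits exposure but does not replace the offer.
- Event start and end times are already annotated, so users can align an event with audio and raw sensor data. This answers any claim that events are attached to the wrong hours. It does not help with an event that was never asked about.

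**Conclusion.** The point holds for the procedure as described. Both call questions stop at the time of the call while recording goes on, so the per-day event annotation covers the day only up to 6 to 8 PM, later audio lacks the deletion offer, and no step closes the last evening.

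The size is uncertain. On the article's 10 to 14 hours of audio, it is about 0 to 5 hours per day for unpaused recording from a 6 to 9 AM start. If recording runs to a bedtime of 10 PM to midnight, it is 2 to 6 hours per day. Start times, pauses and bedtimes are assumptions.

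A reader might infer that evening events are never annotated and evening audio is never offered for deletion. The documents do not support that: evening time before the call is covered, the script is not shown, and the questionnaire may catch some later conflicts. Nor do they support a single fixed share of the day, because a full 16-hour recording day is an assumption that exceeds the reported audio yield.

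**What to change.** 1. Word both call questions as *since our last call* (on day 1, since recording began).
2. Use the event times already collected to assign each event to its own calendar day.
3. Add one item to the day-7 nightly survey or to the recorder-return form, asking for last-evening events and any deletion request.
4. Flag participant-days collected under the same-day wording, so that users know which annotations stop at the call.
5. If the posted script already looks back to the previous call, correct the article's wording and add only the final-evening step.

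The cost is a script edit and one item, with no additional calls. The drawback is a change of wording during data collection, which the flag makes visible. By the article's counts, 149 of the target 400 had finished the 7-day phase, so the change could still reach up to 400 − 149 = 251 participants at that point.

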#### Audio Data

In situ audio is continuously recorded while participants are awake at 24-bit/48 kHz using omnidirectional Lavalier microphones connected to miniature field recorders. Recordings are segmented into smaller, 15-minute-long files to optimize data transfer and increase data processing efficiency.

We have carefully considered legal and ethical issues in proposing these in situ recordings. Audio recordings are governed by wiretapping laws, which vary from state to state. Utah is a single-party consent state, meaning that as long as a study participant consents to be recorded, other individuals captured on those recordings do not need to additionally consent. However, the ethical principles of beneficence, nonmaleficence, autonomy, and justice require that other individuals who may be recorded need to be aware of that possibility and given the opportunity to not be recorded. For these reasons, participants are instructed to wear a badge that states that they are participating in a study that records audio during daily life and will be allowed to pause the recording whenever an individual they come into contact with requests that they do so, or the participant wishes or is required to do so by policy or law [51]. We have used these methods in previous work, and they typically generate 10 to 14 hours of audio per day.

#### Passive Sensor Data

Raw smartphone sensor data are collected using Beiwe, a cross-platform digital phenotyping app created by Onnela and colleagues [25,50]. The Beiwe platform collects raw data generated by smartphone sensors, including, but not limited to, GPS and accelerometry, Wi-Fi connectivity, Bluetooth device scans, phone and screen status, and phone call and SMS text message event logs linked to onboard device contacts. The specific data collected for a participant is determined by the sensors on their smartphone and the policies of the smartphone manufacturer [52].

#### Medical Records

The state of Utah maintains the Utah Population Database (UPDB) and All Payer Claims Database, which are standardized (ie, use the Systemized Nomenclature of Medicine–Clinical Terms), digital archives of medical encounters in the UHealth and IMHC systems, and insurance claims filed in the state, respectively. These databases are generated for research purposes and will be used to verify and augment participant reports. These databases represent a highly unique and valuable opportunity because it is well documented that retrospective reports of psychiatric history incorrectly fail to identify ~25% to 40% of true positives relative to medical records [67]. Relevant records from these databases will be linked to other participant data. UPDB policy dictates that these records will not be shareable, and individuals or entities wishing to access them will have to seek permission directly from the database administrators.

### Planned Data Processing

Raw item responses as well as relevant total and subscale scores from the self-report questionnaires will be created using standard scoring protocols and included for all self-report measures in the final data set. In addition to raw DERS scores, age- and gender-adjusted *t*-scores computed using the methods in [55] will be included in the final data set. Annotations of participants’ most positive and negative daily events will also be available in the data set. To create these, study staff will use the information provided by participants during the daily phone calls to annotate details about their most positive and negative event for each day, including the beginning and end time of the event, and the type (eg, interaction with another person or financial problem) and nature of the event (eg, positive vs negative). Study staff will additionally annotate speaker IDs (eg, participant and female 1), emotional expressions, and communication behaviors (eg, arguing or cooperating) using information from the corresponding recorded audio.

Audio recordings will be processed to generate gold-standard acoustic feature sets used in behavioral signal processing [68] and affective computing [69] research using the openSMILE toolkit [70]. These methods produce 88 acoustic variables that represent frequency-, energy-, and spectral-related aspects of speech and ambient noise. Acoustic variables will be generated over the smallest window of time possible for each variable and downsampled to produce a summary score for each acoustic variable for each 1 second of the recording.

Raw PDD sensor data will be processed using Forest [71], a freely available library for analyzing Beiwe data developed by the creators of Beiwe. Similar to the acoustic variables described above, Forest produces summary variables for each sensor type that quantify a wide range of behavioral and contextual information. For example, outputs of GPS data include time spent at home, total distance traveled, physical circadian rhythm, and the type (eg, shop, restaurant, and place of worship) and duration of locations visited. The location type is generated using information from the open-source platform OpenStreetMap [72] and is particularly valuable for the current data set as it will allow for the creation of a library of geographically referenced place tags that index risky (eg, amenity=bar; amenity=tobacco retailer) and protective (eg, amenity=library; amenity=gym) locations and will increase the potential information value of the database by providing additional context for the passive sensor data streams collected. Another example of the summary features available from Forest includes outputs of call and text logs, the total number of calls received, the total number of unique callers, and the total duration of calls received. Additional details about all summary variables are available on the Forest GitHub page [71]. Summary variables will be generated for each day and included in our final data set.

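### As described, the study's own nightly staff call enters the Android call-log features and, unless the recorder is paused, the acoustic data, with no rule to remove or flag it

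*Protocol article*

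**What the plan says.** All places are in the protocol article.

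- **The call.** Procedures describes "a continuous 7-day period of intensive data collection", which includes "responding to a brief phone call from study staff every evening". In that call staff "ask participants to describe the most positive and negative events from that day". Daily Call With Study Staff places it between 6 PM and 8 PM.
- **The call logs.** Under Passive Sensor Data, the app collects "phone call and SMS text message event logs linked to onboard device contacts". Planned Data Processing lists among the outputs "the total number of calls received, the total number of unique callers, and the total duration of calls received", and adds: "Summary variables will be generated for each day and included in our final data set". Limitations states that call and text logs exist for Android phones only.
- **The audio.** Audio Data says: "In situ audio is continuously recorded while participants are awake". Participants may pause when someone asks, when they wish, or when policy or law requires it. Planned Data Processing reduces the recordings to 88 acoustic variables, with one score per variable per second.
- **The annotations.** Planned Data Processing builds the annotations of each day's best and worst events from what participants say in this call.
- **Release.** Results makes the summary features downloadable without contact with the team. Raw audio and raw sensor data need ethics approval, a stricter agreement and contact.

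No section says that the staff call is removed from, subtracted from or marked in either stream, or that the recorder is paused for it. No section says that it is kept.

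**The concern.** The features are offered as traces of everyday behaviour. A call that the study places at a set time each evening is not everyday behaviour, yet the features are defined as totals, and a total of calls received includes it if it arrives on the logged phone.

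A strictly constant addition would do little harm, since it shifts everyone's level and leaves the ordering intact. Received-call duration is not of that kind: it grows with how much a participant has to tell. Missed and repeated calls also make the count vary between people. If these differences are related to mood, stress or compliance, part of any association found later would reflect the study procedure.

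The audio raises a smaller, separate matter. The call contains prompted talk about the day's main events, and the same talk is the source of the event annotations. A model relating evening acoustics to those annotations could draw on the interview rather than on the event.

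The data set is the product of this study, and the article says that no hypotheses or analytic plans guide it. Planned Data Processing is therefore the natural place for such a rule. Users of the public files cannot split a daily call total into study and non-study parts.

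**Working it through.** The plan gives no figure for the effect of the staff call, so there is none to reproduce. The check sets the passages together and then sizes the effect.

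**Inputs from the article:** one staff call per evening; 7 days; target sample of 400; 10 to 14 hours of audio per day; one acoustic score per second; call logs on Android only.

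**Inputs not in the article (assumed):** k other incoming calls per day; call length of 5 to 15 minutes (the article says only that the call is brief).

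**1. Number of study calls.** 1 × 7 = 7 per participant at full compliance, so at most 7 × 400 = 2,800. Only those to Android phones can reach the call-log features, and the Android share is not stated.

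**2. Share of calls received (Android).** Share = 1/(k + 1).

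| Other incoming calls per day, k (assumed) | Study share |
|---|---|
| 1 | 1/2 = 50% |
| 2 | 1/3 = 33% |
| 3 | 1/4 = 25% |
| 5 | 1/6 = 17% |
| 10 | 1/11 = 9% |

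The daily number of unique callers also rises by one on each answered day.

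**3. Constant or varying.** If all 7 calls are answered once, every Android participant gains exactly 1 call a day, and differences between participants in counts are unchanged. Duration behaves differently. Someone whose calls last 15 minutes gains 15 − 5 = 10 minutes a day over someone whose calls last 5 minutes, or 10 × 7 = 70 minutes over the week, with no difference in their other calls.

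**4. Share of audio (all participants, recorder not paused).**
- Lowest: 5/(14 × 60) = 5/840 = 0.6%.
- Highest: 15/(10 × 60) = 15/600 = 2.5%.
- In rows of the per-second file: 5 × 60 = 300 to 15 × 60 = 900 per day.

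**5. What a user can do without a flag.** Dropping the whole 6 PM to 8 PM window from the acoustic file removes up to 120 minutes, which is 120/840 = 14% to 120/600 = 20% of the day's audio, in order to exclude 5 to 15 minutes. For daily call totals there is no equivalent step in the public files.

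**The case against.** The strongest case against has four parts.

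- **Silence in a condensed article.** The call-log outputs are given as an example, and the reader is referred to the software page for details and to an open-science site for the call script. A filter or an instruction to pause the recorder could be in documentation not shown. This stands as a limit on wording: the article does not say that the call is kept. But features defined as totals include the call unless a rule removes it, and the processing section gives none. The article also does not say which phone is called; the participant's smartphone is the natural reading.
- **Near-constant effect.** For counts, this stands when calls are answered once each. It does not cover duration, or missed and repeated calls.
- **Small share of audio.** This stands. At 0.6% to 2.5% under assumed lengths, whole-day acoustic summaries would barely move. The fixed hour and the overlap with the annotations are the remaining reasons for a flag.
- **Recoverability.** This stands in part. Raw data are obtainable under the stricter agreement and the acoustic scores are per second, but a user of the public daily call totals cannot undo the addition.

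A reader might go further in three ways that the document does not support. One is that every participant's call features are affected; Limitations rules this out for Apple phones, and text-message features are untouched on any phone. Another is that the contamination is known to track mood or stress; no data on missed calls, repeats or call length are given. The third is that the interview leaks the study's outcome into the predictors. No outcome is designated. The article's example is a future diagnosis or treatment, which follow-up questionnaires and medical records would capture, so the overlap concerns the event annotations only.

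**Conclusion.** The point holds in limited form. For Android participants, the daily received-call count, unique callers and received-call duration would, as described, include the study's nightly call. For all participants the acoustic scores would include it unless the recorder is paused.

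The call-log half matters more. The study call may be a sizeable part of calls received (17% to 50% for 1 to 5 other calls a day), the duration feature is not shifted by a constant, and public users cannot reverse it. The acoustic half is small in volume and mainly calls for a marker.

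The sizes rest on assumed call frequency and length, and the number of participants affected in the call logs depends on an unstated Android share. Differential bias is possible and not demonstrated. The point is worth correcting before release, but it does not undermine the data set.

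**What to change.** Add to Planned Data Processing:

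1. Before the daily call-log summaries are computed, calls from study numbers (or calls matched to staff call times) are removed. Alternatively, the received-call summaries are released both with and without them.
2. The per-second acoustic file carries a flag for the staff-call interval, so that users can exclude it.
3. If filtering or pausing already happens, one sentence saying so is enough.

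The cost is a small processing step with no added participant burden. It needs either the list of study numbers or recorded call times, and the article does not describe a time-stamped staff call log. For the 149 participants who had already completed the 7-day phase, the team should check which of the two exists. For later participants, staff can note start and end times.
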